### 12.1.2 DOSE LEVELS

#### Evorpaccept (ALX148)

- Dose level 1: 15 mg/kg weekly
- Dose level -1: 10 mg/kg weekly
- Dose level -2: 5 mg/kg weekly

#### Cetuximab

- Dose level 1: 250 mg/m^2 weekly (following 400 mg/m^2 loading dose)
- Dose level -1: 200 mg/m^2 weekly
- Dose level -2: 150 mg/m^2 weekly

#### Pembrolizumab

- Dose level 1: 200 mg every 3 weeks
- There are no additional dose levels

Once a dose has been reduced for a given patient, all subsequent cycles should be administered at that dose level, unless further dose reduction is required. Dose re-escalation is not allowed.

### 12.1.3 MANAGEMENT OF HEMATOLOGIC TOXICITY

Evorpaccept (ALX148) may cause hematologic toxicity. Hematologic toxicity is uncommon with pembrolizumab and cetuximab.

#### Management of neutropenia and thrombocytopenia

|                       |                                                                                         |                                                         |                                                   |
|-----------------------|-----------------------------------------------------------------------------------------|---------------------------------------------------------|---------------------------------------------------|
| Toxicity a | Hold treatment (evorpaccept [ALX148], cetuximab, and pembrolizumab) until: b | Restart evorpaccept (ALX148) treatment at: c | Restart cetuximab and pembrolizumab treatment at: |
|-----------------------|-----------------------------------------------------------------------------------------|---------------------------------------------------------|---------------------------------------------------|

|                                                                                                           |                                                                |                       |                                                                              |
|-----------------------------------------------------------------------------------------------------------|----------------------------------------------------------------|-----------------------|------------------------------------------------------------------------------|
| Uncomplicated Grade 3 neutropenia (ANC<1000/mm  )                                             | ANC ≥1,000/mm                                      | Same dose level       | Same dose levels (2 nd occurrence: reduce cetuximab 1 dose level) |
| Grade 3 neutropenia (ANC<1000/mm  ) associated with a documented infection or fever > 38.55°C | ANC ≥1,000/mm  and infection is adequately treated | Decrease 1 dose level | Same dose levels (2 nd occurrence: reduce cetuximab 1 dose level) |
| Grade 4 neutropenia (ANC<500/mm  )                                                            | ANC ≥1,000/mm                                      | Decrease 1 dose level | Same dose levels (2 nd occurrence: reduce cetuximab 1 dose level) |
| Grade 4 thrombocytopenia (Platelet count <25,000/mm  )                                        | Platelets count ≥50,000/mm                         | Decrease 1 dose level | Same dose levels (2 nd occurrence: reduce cetuximab 1 dose level) |

- a. Hematologic toxicities should be managed via supportive care (including transfusions) by Investigators' medical judgement.
- b. A treatment delay of more than 14 days (beyond the next scheduled study drug infusion) due to lack of recovery will result in discontinuation of the patient from the treatment unless otherwise agreed between the Investigator and AGICC.
- c. Dose reduction of evorpaccept (ALX148) by 1 and, if needed, 2 dose levels will be allowed depending on the type and severity of toxicity encountered. Patients requiring more than 2 dose reductions will be discontinued from the treatment and entered into the follow-up phase, unless otherwise agreed between the Investigator and AGICC.

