##### *Evorpaccept (ALX148) combination therapy*

In a phase I study presented at ASCO 2019 and updated at ASCO 2020, patients with advanced refractory solid tumors were treated with evorpaccept (ALX148) in combination with pembrolizumab (non-small cell lung cancer (NSCLC) and head/neck squamous cell carcinoma (HNSCC), N=52) or evorpaccept (ALX148) in combination with trastuzumab (HER2+, primarily gastric/gastroesophageal junction carcinoma, N=30). Among patients treated with evorpaccept (ALX148) and pembrolizumab, any grade TRAEs included AST increased (17%), ALT increased (14%), fatigue (12%), anemia (10%), pruritus (10%), rash (10%), infusion reaction (8%), arthralgia (6%), pyrexia (6%), leukopenia (6%), decreased appetite (4%), myalgia (4%), nausea (4%), and neutropenia (4%). Grade  $\geq 3$  TRAEs included thrombocytopenia (4%) and 2% each ALT increased, anemia, and neutropenia. Among patients treated with evorpaccept (ALX148) and trastuzumab, any grade TRAEs included fatigue (30%), thrombocytopenia (17%), decreased appetite (10%), pruritus (10%), pyrexia (10%), anemia (7%), neutropenia (7%), and nausea (7%). Grade  $\geq 3$  TRAEs included thrombocytopenia (7%) and neutropenia (6%).

Any grade TRAEs included fatigue (11%), AST increase (9%), ALT increase (8%), anemia (8%), and thrombocytopenia (6%).

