#### 4.1.5 DOSE-LIMITING TOXICITIES

Adverse events (AEs), serious adverse events (SAEs), and clinically significant laboratory values that occur during the study and considered related to any of the study drugs will be regularly evaluated to determine whether continued dosing would potentially compromise the safety of future subjects. The severity of adverse events will be graded according to CTCAE version 5.0. The following constitute the definition of DLT in this study:

- Hematologic:
  - Grade 4 neutropenia lasting >7 days
  - Febrile neutropenia (defined as neutropenia  $\geq$  Grade 3 and a single body temperature  $>38.3^{\circ}\text{C}$  or a sustained temperature of  $\geq 38^{\circ}\text{C}$  for more than one hour)
  - Grade  $\geq 3$  neutropenia with infection
  - Grade 3 thrombocytopenia associated with clinically significant bleeding
  - Grade 4 thrombocytopenia
  - Grade  $\geq 3$  hemophagocytic lymphohistiocytosis
- Non-hematologic:
  - AST or ALT  $> 3$  x upper limit of normal (ULN) AND total bilirubin  $> 2$  x ULN, unless clear evidence of biliary obstruction exists
  - For patients with hepatic metastases, AST or ALT  $> 8$  x ULN or AST or ALT  $> 5$  x ULN for  $\geq 14$  days
  - Any Grade 2 pneumonitis that does not resolve to Grade  $\leq 1$  within 3 days of the initiation of maximal supportive care
  - Grade  $\geq 3$  toxicities, with the exception of the following:

- Grade 3 nausea/vomiting or diarrhea <72 hours with adequate antiemetic and other supportive care
- Grade 3 pain, rash, or constipation if duration is < 7 days
- Grade 3 fatigue if duration is < 7 days
- Grade  $\geq$  3 electrolyte abnormality that lasts < 72 hours, is not clinically complicated, and resolves spontaneously or responds to conventional medical interventions
- Grade  $\geq$  3 amylase or lipase that is not associated with symptoms or clinical manifestations of pancreatitis
- Grade  $\geq$  3 hypertension that recovers to Grade 2 within 5 days
- Delay by more than 2 weeks in receiving the next scheduled dose due to persisting toxicities attributable to evorpaccept (ALX148)
- In addition, clinically significant or persistent Grade 2 toxicities may be considered a DLT following review by AGICC and the Investigators.
  - A clinically significant laboratory value is one that indicates a new disease process, an exacerbation or worsening of an existing condition, or requires further action(s) to be taken

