b. Examples of self-care activities of daily living include bathing, dressing and undressing, feeding oneself, using the toilet, and taking medications, as performed by patients who are not bedridden.

c. If an event is assessed as a "significant medical event," it must be reported as a serious adverse event.

AEs associated with pembrolizumab exposure, including coadministration with additional compounds, may represent an immunologic etiology. These immune-related AEs (irAEs) may occur shortly after the first dose or several months after the last dose of pembrolizumab/combination treatment and may affect more than one body system simultaneously. Therefore, early recognition and initiation of treatment is critical to reduce complications. Based on existing clinical study data, most irAEs were reversible and could be managed with interruptions of pembrolizumab/combination treatment, administration of corticosteroids and/or other supportive care. For suspected irAEs, ensure adequate evaluation to confirm etiology or exclude other causes. Additional procedures or tests such as bronchoscopy,

endoscopy, skin biopsy may be included as part of the evaluation. Dose modification and toxicity management guidelines for irAEs are provided in Section 12.1 subsections.

AEs should be managed with maximal supportive care per Investigator discretion and based on published guidelines, taking the most likely causative drug into account. In general, no specific dose adjustments or changes to the dose schedule are recommended for Grade 1/2 treatment-related toxicity with several exceptions noted in Sections 12.1.3 through 12.1.9. However, Investigators should always manage their patients according to their medical judgment based on the particular clinical circumstances and utilize the following guidelines.

When study interventions are administered in combination, attribution of an adverse event to a single or multiple compound(s) is likely to be difficult. Therefore, evorpacept (ALX148), cetuximab, **and** pembrolizumab should be interrupted for Grade  $\geq 3$  treatment-related toxicity, unless as otherwise described in Sections 12.1.3 through 12.1.11. Retreatment following treatment interruption for treatment-related toxicity or the start of a new cycle of treatment may begin only if (and as detailed in Sections 12.1.3 through 12.1.11):

- ANC  $\geq 1,000/\text{mm}^3$
- Platelet count  $\geq 50,000/\text{mm}^3$

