- Evidence for Grade  $\geq 2$  hemolysis has returned to baseline or Grade  $\leq 1$  severity (or, at the Investigator discretion, Grade  $\leq 2$  if not considered a safety risk for the patient)
- Non-hematologic toxicities have returned to baseline or Grade  $\leq 1$  severity (or, at the Investigator discretion, Grade  $\leq 2$  if not considered a safety risk for the patient)

Sections 12.1.3 through 12.1.11 detail specific guidelines for the management of common AEs. Other AEs should be managed per published guidelines and Investigator discretion if clearly due to cetuximab or pembrolizumab.

General instructions for dose modification and toxicity management guidelines for immune-related AEs (additional details are provided in Sections 12.1.3 through 12.1.11):

- Severe and life-threatening irAEs should be treated with IV corticosteroids followed by oral steroids. Other immunosuppressive treatment should begin if the irAEs are not controlled by corticosteroids.
- Study intervention must be permanently discontinued if the irAE does not resolve or the corticosteroid dose is not  $\leq 10$  mg/day within 12 weeks of the last study intervention treatment.
- The corticosteroid taper should begin when the irAE is  $\leq$  Grade 1 and continue at least 4 weeks.

- If pembrolizumab has been withheld, pembrolizumab may resume after the irAE decreases to  $\leq$  Grade 1 and the patient is receiving  $\leq 10$  mg/day oral prednisone or equivalent
- Pembrolizumab must be permanently discontinued for  $\geq$  Grade 3 neurologic toxicity,  $\geq$  Grade 2 myocarditis, confirmed Stevens-Johnson Syndrome/Toxic Epidermal Necrolysis/Drug Rash with Eosinophilia and Systemic Symptoms, and other grade 4 or recurrent grade 3 immune-related adverse events.

Patients with grade 4 hypertension must not receive further treatment with cetuximab.

If the toxicity is unlikely due to cetuximab or pembrolizumab, there should be a low threshold to attribute it to evorpaccept (ALX148) and the following guidelines should be used:

- Patients experiencing Grade 3 or 4 potentially treatment related toxicity or intolerable Grade 2 toxicity despite maximal supportive care should have their treatment (evorpaccept (ALX148), cetuximab, **and** pembrolizumab) interrupted. Appropriate follow-up assessments should be performed until adequate recovery occurs as assessed by the Investigator.

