- Treatment may be resumed when toxicities have returned to baseline or Grade  $\leq 1$  severity (or, at the Investigator discretion, Grade  $\leq 2$  if not considered a safety risk for the patient). A treatment delay of more than 14 days (beyond the next scheduled study drug infusion) due to lack of recovery will result in discontinuation of the patient from the treatment unless otherwise agreed between the Investigator and AGICC.
- Upon resuming:
  - Evorpaccept (ALX148) should be reduced by one dose level (Section 12.1.2)
  - Cetuximab and pembrolizumab can be continued at the same dose level (Section 12.1.2). Cetuximab dose may be reduced (Section 12.1.2) per Investigator discretion
  - If a pembrolizumab immune-mediated toxicity is suspected, guidelines for workup and management should be followed. If severe, pembrolizumab can be discontinued per investigator discretion (must discontinue if grade 4 or recurrent grade 3 and likely discontinue if grade 3)

If the AE that led to treatment interruption improves to allow treatment resumption/resolves, then re-dosing in that cycle is allowed. Doses omitted for toxicity are not replaced within the same cycle. If a treatment interruption continues beyond Day 21 of the current cycle, then the day when treatment is restarted will be counted as Day 1 of the next cycle. A treatment delay of more than 14 days (beyond the next scheduled study drug infusion) due to lack of recovery will result in discontinuation of the patient from the treatment unless otherwise agreed between the Investigator and AGICC.

Evorpaccept (ALX148), cetuximab, and pembrolizumab may be interrupted for situations other than treatment-related AEs such as medical / surgical events and/or unforeseen circumstances not related to study intervention. However, intervention is to be restarted within 3 weeks of the originally scheduled dose, unless otherwise discussed with AGICC. The reason for study intervention interruption is to be documented in the patient's study record.

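### Two fever limits for neutropenia: a patient with febrile neutropenia under Section 4.1.5 can be restarted on evorpacept at the same dose under the Section 12.1.3 table

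*Protocol*

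**What the plan says.** Protocol Section 4.1.5 (Dose-Limiting Toxicities) lists febrile neutropenia as a DLT and defines it. The neutropenia must be at least "Grade 3 and a single body temperature" above 38.3°C, or a temperature of 38°C or more that lasts over one hour. The protocol gives no other definition of febrile neutropenia.

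The neutropenia and thrombocytopenia table in Section 12.1.3 has two rows for Grade 3 neutropenia:

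- "Uncomplicated Grade 3 neutropenia": all three drugs are held until the ANC is back to 1,000/mm³, then evorpacept restarts at the same dose level.
- Grade 3 neutropenia "associated with a documented infection or fever > 38.55°C": all three drugs are held until the ANC has recovered and any infection has been adequately treated, then evorpacept restarts one level lower.

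Grade 4 neutropenia has its own row and always brings a one-level decrease. The table does not define uncomplicated and does not refer back to Section 4.1.5.

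Section 12.1.1 (General Guidance) has a broader rule. After a Grade 3 or 4 toxicity that is unlikely to be due to cetuximab or pembrolizumab, evorpacept resumes one level lower. The same section states that "Sections 12.1.3 through 12.1.11 detail specific guidelines for the management of common AEs".

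**The concern.** The protocol applies two fever limits to the same clinical event. The Section 12.1.3 limit is the higher one, and no reason for it is given. A patient can therefore meet the protocol's own definition of febrile neutropenia, an event it counts as dose-limiting, without reaching the row that lowers the dose. The only Grade 3 row left returns the patient to the dose at which the event occurred.

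The consequence is inconsistent dosing. A site that works from the table restarts evorpacept at the same level. A site that treats the Section 4.1.5 definition as the meaning of complicated restarts one level lower.

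**Working it through.** The plan states no figure that needs reproducing. The check sets the two rules side by side and then sizes the gap.

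**Inputs**

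- Section 4.1.5: Grade ≥3 neutropenia with a single temperature >38.3°C, or ≥38°C for more than one hour.
- Section 12.1.3 table: Grade 3 neutropenia is ANC <1,000/mm³ and Grade 4 is ANC <500/mm³. The fever limit for a dose reduction in Grade 3 is >38.55°C, with documented infection as the alternative trigger.
- Section 12.1.2: evorpacept levels of 15, 10 and 5 mg/kg weekly.
- Section 2.3.1: Grade ≥3 neutropenia in 2% of patients on evorpacept plus pembrolizumab and 6% on evorpacept plus trastuzumab.
- Planned sample size: 48.

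**Which patients fall between the rules**

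| Grade 3 neutropenia, no documented infection | Section 4.1.5 | Section 12.1.3 fever row | Evorpacept restart if the table is followed |
|---|---|---|---|
| Single temperature above 38.3 and up to 38.55°C | Febrile neutropenia | Not met | Same dose possible |
| 38.0 to 38.55°C for more than one hour | Febrile neutropenia | Not met | Same dose possible |
| Above 38.55°C | Febrile neutropenia | Met | One level lower |

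The gap is confined to ANC 500 to <1,000/mm³. Grade 4 neutropenia and Grade 3 with documented infection are reduced in any case.

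**Width of the gap**

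- Single reading: 38.55 − 38.3 = 0.25°C.
- Sustained: 38.55 − 38.0 = 0.55°C.
- If 38.55 is a slip for 38.5 (an assumption), the gap is still 38.5 − 38.3 = 0.20°C and 38.5 − 38.0 = 0.50°C.

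**Dose at stake**

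- From level 1: (15 − 10)/15 = 33%.
- From level −1: (10 − 5)/10 = 50%.

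**Number of patients**

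If the Section 2.3.1 rates held for the three-drug regimen (an assumption, because its own rate is not given):

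- 48 × 0.02 = 0.96
- 48 × 0.06 = 2.88

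So about 1 to 3 patients would have any Grade ≥3 neutropenia. At those rates this is an upper bound on the affected group, since Grade 4 events, documented infections and temperatures outside the band all drop out.

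**Whether the general rule closes the gap**

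Section 12.1.3 says hematologic toxicity is uncommon with cetuximab and pembrolizumab, so the Section 12.1.1 rule would point to a reduction for most neutropenia here. But if that rule overrode the table, the same-dose restart in the uncomplicated row would rarely apply. The table therefore has to be read as a specific exception. Section 12.1.1 supports this reading by sending the reader to Sections 12.1.3 through 12.1.11 for the detail of retreatment. A site that follows the table is reading the protocol reasonably.

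**The case against.** The best counter-argument is that DLT criteria and individual dose rules answer different questions and need not match. The two lists already differ elsewhere. Grade 4 neutropenia is a DLT only if it lasts more than 7 days, yet the table reduces evorpacept for any Grade 4 neutropenia. Grade 3 thrombocytopenia with significant bleeding is a DLT but has no row in the table.

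It can also be said that few investigators would call febrile neutropenia uncomplicated. On that reading the patient at 38.4°C fits neither row and the general rule applies, giving the one-level reduction wanted here. The Section 12.1.1 clause "unless as otherwise described in Sections 12.1.3 through 12.1.11" concerns interruption of treatment, not the restart dose. Both Grade 3 rows hold all three drugs until the ANC recovers, so the immediate action is the same. Very few patients would be affected. A lower fever limit also has a price, because "Dose re-escalation is not allowed".

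Much of this stands. DLT status does not by itself require a reduction in the individual patient, the table permits the same-dose restart without compelling it, and the numbers are small. It does not reconcile the two limits. The fever-or-infection row covers the same two complications as adjacent DLT items, and only the fever limit differs, with no reason given. The quoted clause is indeed about interruption, but the retreatment sentence that follows it also defers to the specific sections. Whether the general rule applies turns on a term the protocol leaves undefined.

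**Conclusion.** The inconsistency is real. A patient with Grade 3 neutropenia, no documented infection and a temperature in the band between the two limits has febrile neutropenia under Section 4.1.5, yet can be restarted on evorpacept at the same dose under Section 12.1.3. The difference is one dose level in a small number of patients, probably a fraction of the 1 to 3 of 48 estimated to have any Grade ≥3 neutropenia. That estimate assumes the earlier combination rates carry over; the existence of the gap does not depend on it.

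This is a matter of patient safety and consistency across sites. It does not affect the DLT count, the cohort decisions, the power or the type I error. It should be corrected because the correction is simple and nothing in the protocol supports the higher limit.

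**What to change.** In the second Grade 3 neutropenia row of the Section 12.1.3 table, replace the 38.55°C fever limit with febrile neutropenia as defined in Section 4.1.5. Leave the Section 4.1.5 definition unchanged, and keep adequate treatment of infection as a restart condition where an infection is found. The new wording covers every fever event that the present limit covers, because any temperature above 38.55°C is also above 38.3°C. It also adds the events now in the gap, so none that meets the definition can be read as uncomplicated.

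The cost is one line in the next amendment and no new procedures. A few more patients may have a one-level evorpacept reduction, which is permanent under Section 12.1.2.

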### Management of hemolytic anemia (hemolysis)e

| Event                                                          | Guidance                                                                                                                                                                                                                                                                                                                                                                                                                                                                                                                                                                                        |
|----------------------------------------------------------------|-------------------------------------------------------------------------------------------------------------------------------------------------------------------------------------------------------------------------------------------------------------------------------------------------------------------------------------------------------------------------------------------------------------------------------------------------------------------------------------------------------------------------------------------------------------------------------------------------|
| Grade 1: Laboratory evidence of hemolysis only                 | 
 
Workup and evaluation: 1) Consider new medications and infectious causes; 2) CBC, CMP (including total, direct, and indirect bilirubin), LDH, haptoglobin, reticulocyte count, folate, B12, iron studies, peripheral smear, urinalysis, PT/INR, PTT, autoimmune serology, direct agglutinin testd
 
Continue evorpaccept (ALX148), cetuximab, and pembrolizumab at the same doses
 
Continue with standard monitoring guidelines
 
                                                                                     |
| Grade 2: Evidence of hemolysis and ≥2 g decrease in hemoglobin | 
 
Workup and evaluation as listed in Grade 1
 
Hold evorpaccept (ALX148), cetuximab, and pembrolizumab
 
If autoimmune hemolytic anemia is suspected, administer 0.5-1 mg/kg/d prednisone equivalents, followed by ≥ 1-month taper. Monitor Hgb levels at least weekly until the steroid tapering process is complete.
 
If event resolves to Grade 1 or better within 2 weeks, may consider resuming evorpaccept (ALX148), cetuximab, and pembrolizumab at same doses, if approved by the medical monitora,b,c
 
 |
| Grade 3: Transfusion or medical intervention indicated         | 
 
Workup and evaluation as listed in Grade 1
 
Permanently discontinue study treatments
 
                                                                                                                                                                                                                                                                                                                                                                                                                                                  |

|                                                                       |                                                                                                                                                                                                                                                                                                                                                                                                                                                                                                                                                                                                                                                                                                                                                                                                                                                                                                 |
|-----------------------------------------------------------------------|-------------------------------------------------------------------------------------------------------------------------------------------------------------------------------------------------------------------------------------------------------------------------------------------------------------------------------------------------------------------------------------------------------------------------------------------------------------------------------------------------------------------------------------------------------------------------------------------------------------------------------------------------------------------------------------------------------------------------------------------------------------------------------------------------------------------------------------------------------------------------------------------------|
|                                                                       | 
 
Consider admitting patient
 
Hematology consult
 
If autoimmune hemolytic anemia is suspected, administer prednisone 1-2 mg/kg/d (oral or IV equivalent depending on symptoms or speed of development), followed by <math>\geq 1</math>-month taper. Monitor Hgb levels at least weekly until the steroid tapering process is complete.
 
Consider RBC transfusion. Do not transfuse more than the minimum number of RBC units necessary to relieve symptoms of anemia or to return a patient to a safe hemoglobin range (7-8 g/dL in stable, noncardiac inpatients).d
 
Begin folic acid 1 mg daily.
 
                                                                                                                                                                                                  |
| Grade 4: Life-threatening consequences; urgent intervention indicated | 
 
Workup and evaluation as listed in Grade 1
 
Permanently discontinue study treatments
 
Admit patient
 
Hematology consult
 
IV corticosteroid (prednisone equivalent 1-2 mg/kg/d), followed by <math>\geq 1</math>-month taper. Monitor Hgb levels at least weekly until the steroid tapering process is complete.
 
If no improvement or worsening on corticosteroids or severe symptoms on presentation, initiate other immunosuppressive drugs, such as rituximab, IVIG, cyclosporine, infliximab, MMF, or ATG.
 
Consider RBC transfusion. Do not transfuse more than the minimum number of RBC units necessary to relieve symptoms of anemia or to return a patient to a safe hemoglobin range (7-8 g/dL in stable, noncardiac inpatients).d
 
Begin folic acid 1 mg daily.
 
 |

a. If corticosteroids have been initiated, they must be tapered over  $\geq 1$  month to  $\leq 10$  mg/day oral prednisone or equivalent before study treatments can be resumed. Add prophylactic antibiotics for opportunistic infections.

b. The acceptable length of the extended period of time for which study treatments can be held to allow for corticosteroids to be reduced to  $\leq 10$  mg/day oral prednisone or equivalent must be agreed upon by the investigator and the Medical Monitor.

c. Resumption of study treatments may be considered in patients who are deriving benefit and have recovered from the immune-related event (baseline or Grade  $\leq 1$ ). Patients can be rechallenged with study treatments only after approval has been documented by both the investigator (or an appropriate delegate) and the Medical Monitor.

